#### Demographics and program attendance.

Participants will report demographic characteristics (e.g., age, race/ethnicity, income) and previous weight loss history at baseline. Enrollment in the program will be queried from the respective programs at initial screening to confirm meeting inclusion criteria. Final session attendance dates will be queried from the program at end of study.

#### Stipends and incentives.

Participants will be paid up to 300 USD for completing the study, including 50 USD for each visit. Participants will also be eligible for a reduce initiation fee for the existing 6-month-long community-based weight management program hosted by the University of Kansas Medical Center. For completing Visit 1, participants will be given a wearable device (estimated value 100 USD). These devices can be used during the accelerometer wear periods. However, participants will be told to prioritize wearing the accelerometer during the selected periods.

### Analytical approach

#### Aim 1: Examine the association between variability in individual stress and weight change.

For hypothesis 1a, that high variability in daily stress will be related to less weight loss, linear regression will examine week-0 average and change frequency in daily stress (morning survey) with weight change at week-12 (visit 3) and week-26 (visit 4). For hypothesis 1b, that high variability in daily stress will be related to less physical activity and sleep, multi-level models with logit link function (and binomial distribution) will be used to examine association between week-0 morning stress and same day MVPA and sleep, with an interaction of time/day*morning stress. For exploratory analyses, we will examine the associations of daily stress with MVPA and sleep at other time points (week-6, week-12, and week-26), lagged day effects of stress (i.e., stress on day 1 influencing MVPA and sleep on day 2) to preserve temporal ordering and considering inverse probability weighted marginal structural models, and the outcome of weight change at week-6.

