### Participants, eligibility, and recruitment

This study seeks 50 individuals who are newly enrolled in a community-based weight loss program centered in a metropolitan area of a Midwest state. Participants will be recruited from an existing 6-month-long community-based weight management program hosted by the University of Kansas Medical Center, local Diabetes Prevention Programs and other behavioral weight loss programs in the local area that may range from 6 to 12-months long. These weight management programs typically include trained health educators, 1-hour weekly video meetings, group peer support, structured nutrition plan (low calorie diet), personalized activity recommendations, and behavior change modifications [15]. Prospective participants will be recruited at their initial consultation or orientation visit for their behavioral weight loss program. Flyers will also be presented to participants at their initial visit. Measures were planned to coincide with initial enrollment (week-0), early weight change (week-6), and later weight change measures (week-12, week-26).

To be included, participants must be newly enrolled or plan to enroll in a community-based weight management program, must be over 18 years of age, have body mass index (BMI) ≥30 m/kg^2^, own a smartphone and be willing to download the mobile application to receive text messages [16]. Participants who chose to cease their community-based weight management program involvement after enrolling in the INSTANT study can still participate in later assessments, improving upon past studies which only included individuals who completed their program [17,18]. Indeed, stress may impact continued engagement in a weight management program. Participants will be excluded for being currently prescribed FDA-approved medications for weight loss, treatment for a medical condition that could affect body weight, or impacting stress levels (e.g., antidepressants), a current psychological condition that is untreated, hospitalization for a psychological condition within the past 12-months, or not being on a stable dose of treatment for at least 6-months. Other exclusion criteria are not being fluent in writing or speaking the English language, mobility limitations so they are unable to perform physical activity, and a family member who was previously enrolled or is currently enrolled in the study.

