#### Ecological momentary assessment (EMA).

Participant’s current state and behaviors will be collected using a customizable software (LifePak, LifeData Corporation, Marion, IN). This software is compatible with both Apple and Android iOS delivered phone notifications as reminders, and study surveys will be completed within the app. Questions occur in the same order for all surveys and are provided as supplementary material (S2–S4 Tables) and a detailed account of constructs is provided in Fig 1. Participants will receive six surveys, including four signal-contingent and two fixed surveys (i.e., available for a fixed time period), through the app each day for 14 continuous days as performed by others measuring physical activity [20]. Signal-contingent surveys occurred randomly within fixed 3-hour windows (8:00am–11:00am, 11:00am-2:00 pm, 2:00 pm-5:00 pm, and 5:00–8:00 pm) and expire 45 minutes after the initial reminder. The two fixed surveys include the morning and evening survey; the morning survey will be available for four hours (8:00am-12:00 pm), and three hours for the evening survey (5:00–8:00 pm). These schedules may be shifted for non-traditional schedules, such as shift work, to ensure participants are available to answer these questions during their waking hours. Participants will be provided with three reminders for signal-contingent surveys, including the initial reminder, and reminders at 15-minutes and 30-minutes, if necessary. Participants will be sent reminders for the morning and evening surveys every hour, if necessary. Sampling time frames and prompt strategies were informed by past EMA studies [21,22]. Participants will be expected to complete at least one morning survey and two within-day surveys (~50%) for 5-days [23], with an additional incentive for 7-days in a row as conducted in our preliminary EMA studies.

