#### Primary exposures.

**Variability in stress and coping:** In the morning survey, morning stress and coping will be assessed using questions based on the Daily Health Diary as assessed in past EMA studies [23,24], their own current stress and their perceived ability to cope with stress. Participants will be prompted to indicate the current stress, with response options ranging from 0–10 and 10 indicating higher stress. Participant coping will be queried with a similar question on their ability to manage stress right now, with the same response options and a higher score indicating a higher ability to manage stress.

**Variability in affect:** During signal-contingent surveys, participants will answer a set of five brief questions including positive and negative affective response. Then, participants will complete 5-questions based on how they are currently feeling positive and negative affect based on the Positive and Negative Affect Scale (PANAS), a validated scale which has been adapted in other EMA studies of affect [10,24,25]. These questions will be asked in the same order and are based on previous EMA studies [6,23,26], with response options ranging 1–4, with higher indicating more prevalent feelings of the emotion. An average of the two positive affect questions and three negative affect questions will be calculated. The average positive affect score will be compared for variability in affect.

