#### Aim 2: Examine the association between variability in coping and positive affect and weight change.

To address hypothesis 2, that high variability in coping and positive affect will be related to less weight loss, linear regression will examine week-0 average and change frequency in coping (morning survey) and positive affect (within day survey) with weight change at week-12 and week-26.

Potential covariates for both models include number of ACEs, program compliance (i.e., number of sessions attended), coping mechanisms (number and type), age, and sex. Statistical significance will be set at *p* = 0.05. All available data will be analyzed with a sensitivity analysis for individuals with complete data. Significant weight loss will be seen at 12-weeks (12.7 ± 19.9 kg), and 6-months (12.7 ± 35.2 kg) based on past studies in our community-based weight loss program allowing us to compare weight loss in Hypothesis 1a and 2. [15]

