#### Sample size and power calculation.

Based on past EMA work (*n* = 39), there was an association between daily morning stress and feeding practices (*p* = 0.01) [52]. Considering physical activity and sleep are also impacted by stress [10,11], we anticipate being able to detect an association between stress variability with physical activity and sleep with prescribed amount (*n* = 50). This amount will allow us to compute a random linear regression model with 0.80 power, 0.3 effect size, 0.01 alpha error probability, 0.27 lower critical R^2^, and up to five predictors (such as potential covariates) [53]. Meeting minimum compliance (5-days), we would still have ≥5 observations/participant (≥250 observations) to calculate variability and detect meaningful associations.

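### Change frequency counts how often ratings move, not by how much, so it is a weak predictor for hypotheses about variability; the 250 pooled observations do not strengthen it for the weight regressions

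*Protocol article*

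**What the plan says.** Under Aim 1, the model for Hypothesis 1a is described thus: "linear regression will examine week-0 average and change frequency in daily stress (morning survey"), with weight change at weeks 12 and 26 as outcome. Under Aim 2 the predictors are "week-0 average and change frequency in coping (morning survey) and positive affect (within day survey"). Both hypotheses (Objective and aims) speak of high variability.

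The morning stress item is scored "with response options ranging from 0–10 and 10 indicating higher stress" (Primary exposures). Coping uses the same response range.

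Surveys are sent "through the app each day for 14 continuous days". The compliance floor in the EMA section is: "Participants will be expected to complete at least one morning survey and two within-day surveys (~50%) for 5-days", "with an additional incentive for 7-days in a row".

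The sample size section concludes: "Meeting minimum compliance (5-days), we would still have ≥5 observations/participant (≥250 observations) to calculate variability and detect meaningful associations". The target is 50 participants.

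**The concern.** The exposure named in the hypotheses and the exposure entered in the models differ. Variability is a matter of size; change frequency, read in the ordinary way, is a matter of occurrence. On an eleven-point item most successive ratings differ by something, so the measure is high for nearly everyone and separates people poorly.

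Two things could make this worse. A raw count has a ceiling set by the number of ratings completed, so it can partly stand in for EMA adherence. And a score built from five ratings is noisy, while the reassurance offered, 250 observations in total, is a property of the whole sample and not of any person's score.

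At stake is the primary association. A predictor weakly related to the intended construct pulls its coefficient toward zero, and a null result would then say little about stress variability and weight loss.

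**Working it through.** **Inputs from the article.** 50 participants; 14 days per EMA period; minimum 5 days; one morning rating per day; at least two and at most four within-day ratings per day; item range 0–10.

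**1. The article's own figure.** 50 × 5 = 250. This reproduces. The weight regressions, however, have one row per participant: one mean, one change-frequency value, one weight change. The number of rows is at most 50, and one person's score rests on that person's ratings only. The 250 person-days are relevant to the multi-level models of Hypothesis 1b, where the day is the observation.

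**2. Size is discarded.** Take two people with five mornings each.
- 4,5,4,5,4: changes 4 of 4; mean 4.4; SD = √[(3 × 0.16 + 2 × 0.36)/4] = √0.30 = 0.55.
- 0,10,0,10,0: changes 4 of 4; mean 4; SD = √[(3 × 16 + 2 × 36)/4] = √30 = 5.48.

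Change frequency is identical; the SD differs tenfold.

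**3. Few possible values.** Five ratings give 5 − 1 = 4 successive pairs, so a proportion can only be 0, 0.25, 0.5, 0.75 or 1. If only adjacent calendar days were paired, five days chosen at random from 14 would give on average 13 × (5/14) × (4/13) = 1.4 pairs.

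**4. Ceiling of a count.** 5 − 1 = 4 changes at minimum compliance and 14 − 1 = 13 at full compliance: 13/4 = 3.25-fold, from compliance alone.

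**5. How well each index recovers true variability.** The article gives no within-person SD, no spread of SDs between people and no distribution of completed days, so these are assumptions. Rounded 0–10 ratings were simulated with person-specific SDs. Completed days were either uniform on 5–14 or highly compliant (5 + Binomial(9, 0.75), mean 11.75). The second column adds wider spreads between people.

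| Correlation | Median SD 1–2, log-SD spread 0.2–0.5 | Median SD 1–2, log-SD spread 0.2–0.6 |
|---|---|---|
| Proportion of changes with true SD | 0.14–0.51 | 0.16–0.55 |
| Within-person SD with true SD | 0.52–0.86 | 0.53–0.90 |
| Count with days completed, uniform days | 0.74–0.89 | 0.68–0.91 |
| Count with days completed, high compliance | 0.39–0.61 | 0.34–0.66 |

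In the wider set the count correlates 0.07–0.37 with true SD under uniform days and 0.14–0.52 under high compliance. It follows days more closely than true variability in 18 of 18 scenarios with uniform days and in 14 of 18 with high compliance.

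**6. Five ratings against fourteen** (median SD 1.5, no autocorrelation; log-SD spread 0.2/0.4/0.6). Squared correlation with true SD:

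| Index | 5 ratings | 14 ratings |
|---|---|---|
| Proportion of changes | 0.03/0.08/0.09 | 0.08/0.19/0.19 |
| Within-person SD | 0.20/0.46/0.58 | 0.45/0.73/0.78 |
| RMSSD | 0.16/0.39/0.51 | 0.36/0.65/0.73 |

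**7. What attenuation costs (illustration only).** Read the stated effect size of 0.3 as R² and suppose that all of it came from true variability. Observed R² is then 0.30 × squared correlation. With N = 50, five predictors and the analysis alpha of 0.05:
- squared correlation 1: R² 0.30, power 0.917
- 0.5: R² 0.15, power 0.537
- 0.2: R² 0.06, power 0.208
- 0.1: R² 0.03, power 0.118

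**The case against.** **The article does not define change frequency.** It gives neither count nor proportion, nor the size of difference that qualifies as a change. A size threshold would carry some information on magnitude, and a separate analysis plan may supply one. This stands as a limit: the point is not that a definition is missing, but that the measure as named, under either ordinary reading, is a poor match to the hypotheses.

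**A count need not mainly measure adherence.** A reader might infer from the 4-to-13 ceiling that it does. The article does not support that without a condition. Fourteen days are planned, seven in a row earn an incentive, and participants are contacted during the period to keep compliance up. With high compliance the link to days is moderate. Nor can one infer that the count would produce a reversed association with weight loss: that needs a correlation between EMA adherence and weight loss, for which the article gives no figure.

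**Safeguards exist.** Aim 2 lists program compliance as a potential covariate and plans a sensitivity analysis in people with complete data. The first is sessions attended, which is a different quantity from EMA days. The second removes the count problem only if complete data includes EMA.

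**The sample size section already powers the regression on 50.** Correct. One might infer that the study treats 250 as its sample size, and it does not. The fault is narrower: the same paragraph offers 250 observations as the reason why five days suffice to calculate variability.

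**Positive affect is different.** Two surveys on five days give at least 10 ratings, so the five-rating point does not reach it, and the simulation of a 0–10 morning item does not describe its 1–4 scale. Only the loss of size carries over.

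**Conclusion.** The point holds in this form. That change frequency ignores the size of changes, and that pooled ratings do not improve a person-level score, follow from the text and need no simulation. The extent of the loss rests on assumptions: across those tried with log-SD spreads of 0.2–0.5, correlation with true variability is about 0.14–0.51 for the proportion of changes and about 0.52–0.86 for the within-person SD. The link between a count and EMA adherence is conditional on the measure being a count and on compliance being uneven. The five-rating imprecision concerns morning stress and coping only, and five is the floor rather than the plan. The power figures show direction and order of size; they are not a forecast.

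**What to change.** **Aims 1 and 2.** Replace change frequency with the within-person SD of the week-0 ratings, or RMSSD with a stated rule for skipped days. Keep the person mean in the model, as already planned. Add the number of EMA ratings completed as a covariate, or run a sensitivity analysis restricted to participants with more completed days. A mixed-effects location-scale model is an option, not a requirement.

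**Sample size and power calculation.** State that five days is the minimum for inclusion, that the participant is the unit of analysis for Hypotheses 1a and 2, and that the 250 person-days relate to the multi-level models of Hypothesis 1b.

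**Cost.** Wording and a little extra analysis; no new data. With nine participants enrolled by January 2026 and results expected in 2027, the change can be prespecified before analysis. It is not a complete cure: scores from five days stay imprecise even with the SD (squared correlation 0.20–0.58 in step 6).

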Investigating daily psychological factors and obesity-related behaviors using EMA across a weight loss intervention may inform creation of an adaptive intervention. Data collected from EMA methodologies can lead to adaptive mHealth interventions, including ecological momentary interventions (EMI) which provide in-the-moment support based on self-report or device feedback to prevent behavior relapse [12]. One possible option where EMA may be used to promote behavior change is physical activity. Engaging in physical activity can be used to cope with stress, suggesting an EMI could propose physical activity amongst low coping times, and promote weight loss [13]. Investigating these claims while an individual is undergoing behavior change (i.e., weight loss) may help identify if these behaviors are valuable focus points for future adaptive weight loss interventions.

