### Objective and aims

The overarching aim of this study is to elucidate potential pathways of stress and stress-related concepts with subsequent health behaviors during a behavioral weight loss intervention. The primary exposure is the difference (i.e., variability) in signal-contingent survey stress, coping, and affect early in the program. The primary outcome is weight change across a behavioral weight loss program, and secondary outcomes are physical activity and sleep. We hypothesize that high variability in daily stress will be related to less weight loss across the initial (12-weeks) and full (26-weeks) program (Hypothesis 1a). Our second hypothesis is that high variability in daily stress will be related to less physical activity and sleep across the initial and full program (Hypothesis 1b). These hypotheses were constructed as higher variability and fluctuations aligns with past literature that with individuals who experience lower stressful daily events and who are able to cope consistently and easily with this daily stress may be more active and lose more weight compared to individuals experience daily changes in stress and are less able to cope or find it difficult to do so [5,14]. Finally, we hypothesize that high variability in coping and positive affect will be related to less weight lost across the initial and full program (Hypothesis 2).

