#### Baseline (week-0).

In the first visit, written consent will be obtained from the participant prior to performing study procedures. Height and weight will be assessed by a trained staff member. The participant will complete questionnaires and will be fitted with an accelerometer to wear for 14-days. Participants will also be provided a 5-day salivary cortisol kits. The procedures for collecting, storing and transporting the saliva samples will be explained by trained staff in additional to the participant watching a short tutorial on the collection process and provided with written instruction. Participants will have the EMA app downloaded to their phone, and receive a tutorial on the app. Beginning the next day after the baseline visits, the participant will respond to EMA prompts for 14-consecutive days and wear the accelerometer. After 14-days, participants will return their accelerometer and saliva kit and delete the EMA app off their phone.

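### The Hypothesis 1b model has one undivided morning-stress term and a stress-by-day interaction that no hypothesis uses: unless day is centred and stress is split, its coefficients do not isolate a same-day effect, and neither measures variability

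*Protocol article*

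**What the plan says.** The Objective and aims section states that "high variability in daily stress will be related to less physical activity and sleep across the initial and full program (Hypothesis 1b"). The exposure is therefore variability, a property of a person over several days.

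Under Aim 1 of the Analytical approach, the form of model for this hypothesis is given as follows: "multi-level models with logit link function (and binomial distribution) will be used". The stated task of these models, and the terms they carry, come next: "examine association between week-0 morning stress and same day MVPA and sleep, with an interaction of time/day*morning stress". The exploratory analyses come in a separate sentence (other time points, lagged effects, week-6 weight change). The interaction is not among them, so it belongs to the main model.

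Hypothesis 1a in the same section is handled differently: "linear regression will examine week-0 average and change frequency in daily stress (morning survey) with weight change". Hypothesis 2 uses the same pair of person-level terms for coping and positive affect.

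Morning stress is a single rating: "Participants will be prompted to indicate the current stress, with response options ranging from 0–10 and 10 indicating higher stress". On timing: "Beginning the next day after the baseline visits, the participant will respond to EMA prompts for 14-consecutive days". The article does not say how day is numbered, whether stress is centred, or which coefficient decides Hypothesis 1b.

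**The concern.** Three features of the model as written matter.

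- **Interaction.** With a stress-by-day product in the model, the stress coefficient is the association where day equals zero, and the product measures change in that association across days. If stress has a steady same-day association, the product is at its null and the day-zero coefficient is an imprecise estimate at the edge of the data or outside it.
- **Undivided stress.** A single daily stress term mixes two questions: whether a person is less active on a worse-than-usual morning, and whether generally more stressed people are less active. The Introduction motivates the study by interventions that "provide in-the-moment support based on self-report or device feedback to prevent behavior relapse". Only the first question bears directly on that.
- **Level, not variability.** Neither the stress term nor its product with day measures how variable a person's stress is.

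A real same-day association could be missed, a between-person difference could be read as a momentary one, and the hypothesis as worded could go untested.

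**Working it through.** **Inputs from the article.** "This study seeks 50 individuals who are newly enrolled in a community-based weight loss program"; 14 days per assessment period; stress scored 0-10; significance at 0.05. The sample size section describes a linear regression, not this multilevel logistic model, so there is no stated figure to reproduce here. Intraclass correlations, variances and effect sizes are not given; those below are assumptions.

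**Step 1: cost of uncentred day.** For a steady association, the variance of the stress slope at day 0 relative to mid-window is 1 + mean(day)²/var(day). The variance of 14 consecutive integers is (14² − 1)/12 = 16.25.

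- Days 1-14: 1 + 7.5²/16.25 = 4.46; standard error ratio √4.46 = 2.11.
- Days 0-13: 1 + 6.5²/16.25 = 3.60; ratio √3.60 = 1.90.

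An 80% power test has expected z = 1.96 + 0.84 = 2.80. Dividing gives 2.80/2.11 = 1.33 and 2.80/1.90 = 1.47, so power from within-person information alone is about 26% and 31%.

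**Step 2: simulated power, constant same-day effect, 50 people, 14 days.** The linear runs use a random intercept, intraclass correlations of 0.4 (stress) and 0.5 (outcome), and 800 replicates. The logistic runs use generalised estimating equations with independence working correlation as a stand-in for the multilevel logit, and 200 replicates.

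| Model | Linear | Logistic |
|---|---|---|
| No interaction | 0.80-0.81 | not run |
| Undivided stress, days 1-14 | 0.34 | 0.15 |
| Undivided stress, days 0-13 | 0.40 | 0.16 |
| Undivided stress, day centred | not run | 0.49 |
| Split stress, days 1-14 | not run | 0.36 |
| Split stress, day centred | 0.82-0.83 | 0.96 |

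The interaction rejected 6-7% in the linear runs and 4-9% in the logistic runs, close to its null rate. A second linear check fell from about 75% to 35%.

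**Step 3: blending.** The logistic runs set between- and within-person standard deviations both at 1.5, so under independence weighting the within-person share is 1.5²/(1.5² + 1.5²) = 0.5. A within-person effect of −0.2 with no between-person effect should give about 0.5 × (−0.2) = −0.10 (simulated −0.09). A between-person effect of −0.4 with no within-person effect should give about −0.20 (simulated −0.18).

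Rejection rates when the true within-person effect is zero:

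| Setting | Undivided stress | Deviation term |
|---|---|---|
| Linear, no interaction, between-person r = −0.5, 14 days | 11-23% | 3-7% |
| Same, 5 days | 20-39% | 3-7% |
| Linear, no interaction, r = −0.3, 14 days | 8-10% | 3-7% |
| Same, 5 days | 9-17% | 3-7% |
| Logistic, with interaction, days 1-14 | 60% | 8% |
| Logistic, with interaction, day centred | 95% | 7% |

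A second linear check without the interaction, at r = −0.5, gave about 12% (14 days) and 19% (5 days). With the interaction kept as written, inflation in linear runs was only about 7-10%, because the day-zero coefficient is too imprecise to reject often. The logistic stand-in weights between-person information more heavily than a random-intercept model would, so its 60% and 95% should be read as high.

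**Step 4: variability.** In logistic runs (400 replicates, day centred) where only each person's stress standard deviation drove the outcome, the stress term rejected 7.5% and the interaction 4.8%, against null rates of 6.8% and 7.3%. A person-level standard deviation term rejected 99% (9% under its null).

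**The case against.** The strongest reply is that the article fixes neither the day coding nor the form of the stress term. Centring, coding and the deciding contrast usually belong in an analysis plan, which is not shown, and their absence from a condensed article is no fault. With day centred and stress split, the same multilevel structure does estimate the average same-day association.

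That reply stands, and it rules out a stronger reading. A reader might infer that the interaction alone stops the model from testing any same-day association, or that the study will lose most of its power. The documents do not support this: it requires day to be uncentred and the day-zero coefficient to be taken as the result, and the article says neither.

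It is also fair that Hypothesis 1b concerns variability, a person-level exposure, so between-person information does not contaminate the hypothesis as worded. The within-person question comes from the study's stated use, and the Discussion claims no more than that results may inform a future intervention.

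What remains is what the article does fix: a drift term that serves no hypothesis sits in the main model, stress is described as a single term, and no variability term appears, although Hypotheses 1a and 2 have one. The first two can be improved at little cost, and no coding of the present terms repairs the third.

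**Conclusion.** The point holds in conditional form and is worth acting on. If day is uncentred, the standard error of the stress coefficient is 1.9 to 2.1 times that at mid-window. This is algebra for a 14-day window and a steady association, and rests on no assumed variance. If stress is undivided, its coefficient cannot separate a momentary association from a difference between people.

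The simulated power and error rates are illustrative only. They rest on assumed intraclass correlations, variances and effects. The main runs use a linear outcome where the protocol specifies a logit link, and the logistic runs have 200-400 replicates (at 200, the standard error of a rate near 0.5 is √(0.25/200) = 0.035). Most of the linear false-positive figures come from a model without the interaction; under the model as written the inflation is modest.

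The level-for-variability mismatch does not depend on coding. Centring repairs the same-day test but does not create a test of Hypothesis 1b as worded.

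**What to change.** In the Aim 1 text for Hypothesis 1b:

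1. Enter morning stress as two terms: the daily deviation from the person's own week-0 mean, and that week-0 mean.
2. Keep day as a main effect. Either move the stress-by-day product to the exploratory analyses, or centre day at mid-window (7.5 for days 1-14) so that the stress coefficient is the average association.
3. State that same-day conclusions rest on the deviation term and between-person conclusions on person-level terms.
4. Add the person-level variability measure already used for Hypotheses 1a and 2 (change frequency) and decide Hypothesis 1b on it, or report the same-day result as a separate question.

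This takes a few sentences and no new data. The cost is one or two extra person-level coefficients among 50 participants. Person-level summaries will also be noisy for anyone near the 5-day compliance minimum. Moving the interaction gives up a confirmatory drift test that no hypothesis calls for. The Current progress section reports nine participants enrolled by January 2026, so the change can still be made well before the analysis.
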